## Abstract

**Background:**

The World Health Organization (WHO) has included comorbidity between depression and a chronic disease among the 10 leading global health priorities. Although there is a high prevalence of multimorbidity, health care systems are mainly designed for the management of individual diseases. Given the difficulty in delivering face-to-face psychological treatments, alternative models of treatment delivery have been proposed, emphasizing the role of technologies such as the Internet. The aim of this study is to assess the efficacy in Primary Care (PC) of a blended low-intensity psychological intervention applied using information and communication technologies (ICTs) for the treatment of multimorbidity in PC (depression and type 2 diabetes/low back pain) by means of a randomized controlled trial (RCT). Our main hypothesis is that improved usual care combined with psychological therapy applied using ICTs will be more efficacious for improvement in the symptomatology of multimorbidity, compared to a group with only improved treatment as usual six months after the end of treatment.

**Methods:**

A protocol has been designed combining a face-to-face intervention with a supporting online programme that will be tested by an RCT conducted in three different regions (Andalusia, Aragon and the Balearic Islands). The RCT will evaluate three hundred participants diagnosed with depression and type 2 diabetes/low back pain. Four highly experienced research groups specializing in clinical psychology are involved in this trial, and there will be ample possibilities for translation and transfer to usual clinical practice.

**Discussion:**

This clinical trial will lead to improvement in financial sustainability, maximizing the use of resources and responding to principles of efficiency and effectiveness. Furthermore, based on the evaluation of the feasibility of implementing this intervention in primary care facilities, we expect to be able to suggest the intervention for incorporation into public policy. In conclusion, positive results of this study could have a significant impact on one of the most important health-related problems, multimorbidity.

**Trial registration:**

ClinicalTrials.gov, NCT03426709. Registered retrospectively on 08 February 2018.

## Background

Multimorbidity, the presence of two or more medical conditions of long duration, is a prevalent finding, reaching levels of approximately 23% in European countries and increasing with age until it constitutes the norm in people aged 65 years and over [1]. However, the structure of health systems and those of medical research and education is designed for the prevention, treatment and management of isolated diseases and not multimorbidity.

The only meta-analysis to look at the efficacy of comorbidity treatment analysed 9 randomized controlled trials (RCTs), most of them in elderly patients [2]. The interventions consisted of a change in the provision of care (case management or interdisciplinary collaboration) or patient-oriented interventions. Information and communication technologies (ICTs) were not used in any of the cases. The results indicate that it is difficult to improve outcomes in this population, but those interventions that focus on specific risk factors or difficulties may be more effective. An important limitation in the literature is that no cost-effectiveness studies were included, nor was there any inclusion of qualitative studies attempting to understand the barriers in the interaction between health systems and patients [2]. In addition, changes in the provision of medical services are more complex and costly, making them less sustainable over time than personalized interventions. However, forms of personalized intervention based on ‘stepped care’ models and using ICTs have not been evaluated in multimorbidity.

Current guidelines for the treatment of comorbidity emphasize the need to personalize treatment, after an individualized evaluation of the disorders and their context, as well as to negotiate the therapeutic goals with the patients and re-evaluate them throughout the process, a process denominated the ‘Ariadne Principles’ [3]. All of this requires communication skills and time availability which not always possible in current health systems [4]. Therefore, complementary strategies are required to support general practitioners (GPs) in the provision of personalized and appropriate care to these patients [1].

The few studies published on multimorbidity in Spain, mainly in the elderly population, confirm that the negative impact on quality of life and disability is largely caused by mental disorders [5], more specifically depression [6]. This represents an important worldwide public health problem, as it is estimated that it will be the second leading cause of disability in the world by 2020 [7], with a very high economic cost [8]. Owing to its huge prevalence, 13.9–29% in primary care (PC) [9], international health authorities consider that available economic resources will be unable to meet the psychological treatment needs of this population [10]. For this reason, innovative and cost-effective alternatives that make use of ICTs for the treatment of depression and involve minimal face-to-face services are being proposed. The use of ICTs has proven effective both for depression and different mental health problems [11]. Therefore, prestigious organizations such as the National Institute of Clinical Excellence (NICE) in the UK have included in their guide [12] for online treatments such as Beating the Blues to treat depression.

Meta-analyses confirm that the two interventions of first choice for depression are pharmacotherapy and/or psychotherapy. The results are similar in the short term, but higher in the long term for psychological treatments, with lower dropout rates and fewer relapses [13, 14]. Different national and international clinical guidelines [12, 15] have proposed a stepped care model in PC, whereby a large proportion of patients are treated first with low-intensity interventions, with significant clinical benefits. In depression, low-intensity interventions are offered to patients with mild or moderate depressive symptoms.

The World Health Organization (WHO) has included comorbidity between depression and a chronic medical disease among the 10 leading global health priorities [5]. The comorbidity between depression and somatic illness means a significant increase in the disease burden since it implies a greater number of symptoms, higher morbidity, higher health care costs and a worse functioning and quality of life [16]. Current evidence supports a bidirectional relationship between depression and medical illness [17]. The suggested mechanisms to explain this complex relationship would include both biological aspects and behavioural variables. Depression is also associated with worse adherence to treatment in patients with comorbidity, for example, in antihypertensive or diabetes treatment [18, 19].

As regards medical conditions, although hypertension is highly prevalent (50–60%) [5], the most disabling conditions are osteoarticular diseases, diabetes and cerebral infarction [5, 6]. Therefore, the study will focus on two physical conditions comorbid to depression that involve the greatest disability, loss of quality of life and higher health costs: diabetes and chronic pain.

In 2013, the International Diabetes Federation (IDF) [20] reported that 382 million people in the world had diabetes, estimating that 592 million people will have diabetes by 2035, which would mean an increase of 55%. In terms of healthcare provision, it is estimated that in 2013, 548 billion dollars were spent worldwide on the care of diabetes and its complications, a rate that will increase over the years. The risk person with diabetes has of suffering from depression is approximately double that of a person without diabetes [21]. One in four patients with diabetes has depression [22], with higher mortality in these patients [23], and therefore depression and diabetes should be treated together and not as isolated diseases [23]. A review on the effectiveness of depression treatments in patients with diabetes [24] confirmed that it is effective, more specifically psychotherapy combined with self-care education for patients, with improvements shown in both psychological variables and glycaemic control.

Finally, the comorbidity of depression and chronic pain is extremely high in PC (56%) and reaches even higher rates in secondary care (50–69%) [25]. Given the high level of disability associated with the comorbidity of chronic pain and depression, and regardless of the direction of this association, national guidelines and consensus [15, 25] indicate the need to perform an objective assessment of pain in patients with depression by means of validated instruments. In addition, they establish that an integral therapeutic intervention should be considered, contemplating pharmacological and non-pharmacological treatments. The most common pain affects the lumbar skeletal muscle and is of mechanical origin, and almost the entire population suffers from it sometime in their life [26]. Together with depression, they lead the ranking of global disability caused by diseases [27]. Clinical guidelines recommend a treatment that includes education, physical exercise, physiotherapy and acupuncture [28]. However, there is not enough evidence on long-term results or on the superiority of any of these treatments over others [29–31]. A recent systematic review with meta-analysis has found long-term superiority of cognitive behavioural therapy compared to other therapies in relation to pain, disability and quality of life [32]. Despite the advantages that they could bring, there are no studies on the application of ICTs to either multimorbidity or any of the medical conditions included in this study [33].

The aim of this study is to evaluate the effectiveness in PC of a blended low-intensity psychological intervention applied through ICTs in the treatment of multimorbidity in PC (depression and type 2 diabetes / low back pain) in an RCT. Our main hypothesis is that the treatment-as-usual intervention, enhanced through the delivery of low-intensity psychological therapy by ICTs, will be more effective for the improvement of the symptomatology of multimorbidity in PC, in relation to a group with treatment-as-usual only, measured at 6 months after completion of the treatment.

## Methods

### Study design

This study is a two-armed and multicentre RCT, coordinated by the Aragon’s group. Participants will be randomly allocated to one of two conditions: a) low intensity Internet-delivered psychological intervention and b) improved treatment-as-usual (iTAU) groups in primary care.

### Setting and study sample

Participants will be recruited from PC health centres in the three Spanish regions participating in the study (Andalusia, Aragon and the Balearic Islands) from patients who meet the inclusion criteria and to whom the characteristics of the study will be explained. Patients will be recruited by GPs working in these PC centres until the required sample is completed, with a quota of 100 patients assigned to each centre. The inclusion and exclusion criteria are given in Table 1.

**Table 1 Tab1:** Inclusion and exclusion criteria

Inclusion criteria	Exclusion criteria
Minimum age of 18 years	Any diagnosis of a disease that may affect the central nervous system (brain condition, traumatic brain injury, dementia, etc.)
DSM-5 diagnosis of Major Depression or persistent depressive disorder, mild or moderate depression expressed as a score lower than 14 in the Patient Health Questionnaire (PHQ-9)	Other psychiatric diagnoses or acute psychiatric illness (substance dependence or abuse, history of schizophrenia or other psychotic disorders, eating disorders, etc.), except for anxiety disorder or personality disorders
Ability to understand oral and written Spanish	Any medical, infectious or degenerative disease that may affect mood
Willingness to participate in the study and signing informed consent	Presence of delusional ideas or hallucinations whether consistent or not with mood
Duration of depressive symptoms 2 months or more	Suicide risk
Diagnosis of one of the following two conditions: - Type 2 Diabetes (Diagnosis according to criteria of the American Diabetes Association, ADA) - Lower back pain (Diagnosis of non-specific chronic low back pain according to the definition established by the CPG COST B-13 with a duration of at least 6 months)	
Possession of and ability to use a computer, an Internet connection and a mobile phone	

### Sample size

The sample size of this study was based on the possibility of detecting differences between the intervention programme versus treatment-as-usual, for a difference in the main variable of at least 0.5 standard deviations. This effect size was obtained from other studies, and it is considered a clinically relevant criterion [34, 35]. Assuming equal variance between the groups, a power of 80%, and a level of significance of 5%, 63 subjects were estimated for each group. To be able to compare the subjects treated with the specific intervention versus those receiving with treatment-as-usual only, as well as depending on the conglomerate to which they belong (each disease group), 4 groups were estimated with 63 subjects in each one, with a total of 252 subjects. An experimental mortality loss of 15% was estimated [36, 37], so the required size was finally 300 subjects (100 at each PC centre).

### Recruitment

Participants will be recruited in PC settings by participating GPs from patients fulfilling study criteria. When potential patients are identified by a GP, the characteristics of the study will be explained to them, and if the patients are interested in participating, they will be asked to sign an informed consent. The GPs will complete referral forms, indicating that the patients meet the criteria and will provide a brochure to present the study and an information sheet. The GPs will send the referrals and the patients’ signed consent forms by e-mail to the local researcher. The assessor researcher will contact the participants to agree on the established evaluation times. Some patients may prefer to postpone their decision to participate in the study, in which case they will be provided with information about the study by their GPs and how to contact the research team (by phone, email, or by leaving their information on the website).

The assessor researcher will clarify any doubts, ensure that the participants have read the information about the study, and make sure that they have understood the two experimental conditions. Then the assessor will determine their inclusion in the study from the psychological tests and biological variables related to the inclusion criteria before contacting an independent researcher to implement randomization. This researcher will be unaware of the characteristics of the study. Recruitment will be done consecutively until the final sample sizes are reached.

### Randomization, allocation and masking of study groups

At such a time, the assessor will collect the baseline data and contact a person independent of the research group to perform the individual randomization and inform the assessor of a code that corresponds to the type of treatment (unknown by the assessor) and send it to the researcher with the baseline data. Another independent person will do the data monitoring with a general practitioner. The randomization will be conducted by blocks of patients from the three PC centres, with 100 patients selected from each centre so that 150 patients are randomized into each of the two arms. Participants agree to their inclusion before finding out the treatment to which they will be allocated. All participants will be free to withdraw from the treatment at any time.

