### Analysis strategy

#### Analysis of clinical efficacy

Intention-to-treat and per-protocol analysis will be used. Analysis will include the description and ‘head-to head’ comparison between the two groups. Descriptive statistics of the included variables (mean and 95% confidence interval for normally distributed quantitative variables; and median and interquartile range for abnormally distributed quantitative variables) will be performed. To confirm the main hypothesis, all variables will be compared (t0-tk) using an analysis of variance (ANOVA) and post-hoc tests or Kruskal-Wallis non-parametric tests. Finally, more sophisticated multivariate analysis, including multilevel regression, will be used. The effect size of improvement and the number needed to treat (NNT) in each arm will be estimated.

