#### Cost-utility analysis

Cost-effectiveness will be explored through the calculation of incremental cost-effectiveness ratios (ICERs) for the intervention group using the iTAU group as the control. To estimate the ICER (ratio between incremental costs and incremental effectiveness) the following equation will be used:$$ ICER=\frac{Cost\kern0.17em active\kern0.17em intervention\ group\hbox{-} Cost\ control\ intervention\ group}{Effectiveness\ or\ Utility\ active\ intervention\ group\hbox{-} Effectiveness\ or\ Utility\ control\ intervention\ group\ } $$

Cost-utility will be explored through the calculation of incremental cost-utility ratios (ICURs), which are defined as the ratio between incremental costs and incremental effects measured on QALYs [58]. QALYs will be approximated by using the area-under-the-curve technique.

Data collection will be performed using Excel software and statistical analysis will use SPSS (SPSS Inc., Chicago, IL, USA) software version 20, licensed by the University of Malaga.

Frequency and proportions will be used for descriptive statistics of categorical or qualitative variables. For quantitative variables, the mean and standard deviation will be obtained.

Inferential statistical analysis will use the Chi-square test for qualitative variables, one-way ANOVA test for qualitative and quantitative variables and Student’s t-test for quantitative variables. In all cases, statistical significance will correspond to a value of *p* < 0.05.

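### Randomization is blocked by centre, but no named test gives centre a role; if outcomes differ between centres, the analysis is mildly conservative and loses a little power

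*Protocol article*

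**What the plan says.** The section on randomization, allocation and masking describes individual randomization and says: "The randomization will be conducted by blocks of patients from the three PC centres, with 100 patients selected from each centre". The target is 150 per arm, which means 1:1 allocation, with centre as the natural blocking factor. No block size is given.

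The section on analysis of clinical efficacy names the test of the main hypothesis: "To confirm the main hypothesis, all variables will be compared (t0-tk) using an analysis of variance (ANOVA) and post-hoc tests or Kruskal-Wallis non-parametric tests". It then adds: "Finally, more sophisticated multivariate analysis, including multilevel regression, will be used". It does not say what the levels of that regression are, or that the regression decides the main hypothesis.

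A general list of tests stands under the heading Cost-utility analysis: "Inferential statistical analysis will use the Chi-square test for qualitative variables, one-way ANOVA test for qualitative and quantitative variables and Student’s t-test for quantitative variables". These tests are not called confirmatory. The surrounding text on software, descriptive statistics and the significance level reads as general, and this is the only place where a test for categorical data is named.

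Nowhere does the article name centre as a factor, covariate, stratum or level in an analysis.

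**The concern.** An analysis should follow the randomization. Blocking within centre removes between-centre variation from the true sampling variance of the arm difference. A test that ignores centre still counts that variation in its estimated variance. Its standard error is then larger than it should be, its intervals are too wide and its p-values too high, by an amount that depends on how far the centres differ.

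What is at stake is precision that the design has already paid for. The three centres lie in different regions, so some difference in outcome level is plausible, but the article gives no figure for it. Four of the named tests (one-way ANOVA, t-test, Kruskal-Wallis and the ordinary chi-square) have no place for a blocking factor. An analysis plan that used centre would have to replace them, so more than a missing detail is involved.

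**Working it through.** **1. The plan's own figure.** Inputs from the Sample size section: difference 0.5 SD, power 80%, significance level 5% (sidedness not stated; two-sided is taken here). Normal approximation:

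n per group = 2 × (1.960 + 0.842)² / 0.5² = 62.8, so 63.

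4 × 63 = 252, and 252 / 0.85 = 296.5, so 297 against the stated 300. The sample size reproduces and is not affected by this point.

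**2. Formulas.** Let r be the share of outcome variance that lies between centres, with total variance 1, n patients per arm and exact balance of arms within centre.

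- Standard error reported without centre: √(2/n)
- True standard error: √(2(1 − r)/n)
- Ratio: 1/√(1 − r)
- True type I error at nominal 5%, two-sided: 2 × (1 − Φ(1.96/√(1 − r)))

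The article gives no r, so a range is assumed.

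| r (assumed) | SE ratio | Type I error without centre |
|---|---|---|
| 0 | 1.000 | 5.0% |
| 0.01 | 1.005 | 4.9% |
| 0.02 | 1.010 | 4.8% |
| 0.05 | 1.026 | 4.4% |
| 0.10 | 1.054 | 3.9% |
| 0.20 | 1.118 | 2.8% |

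A simulation of 300 patients, split 50:50 within each of three centres (20,000 replicates per setting), gave 4.8%, 4.8%, 4.6%, 4.2%, 3.7% and 2.7% without centre, and 4.7% to 4.9% throughout with centre as a fixed factor.

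**3. Power where it is near 80%.** With n = 63 per arm and 0.5 SD, the reported SE is √(2/63) = 0.1782.

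- r = 0.05: true SE = 0.1782 × √0.95 = 0.1737. Without centre: Φ((0.5 − 1.96 × 0.1782)/0.1737) = 80.7%. With centre: Φ(0.5/0.1737 − 1.96) = 82.1%. Gain 1.4 points.
- r = 0.10: true SE = 0.1690. 81.4% against 84.1%. Gain 2.7 points.
- r = 0.02: 80.4% against 80.9%. Gain about 0.5 points.

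Simulation (40,000 replicates, 21 per arm per centre) agrees: 79.7% against 81.3% at r = 0.05, 80.3% against 83.2% at r = 0.10, and 80.0% against 80.6% at r = 0.02.

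**4. Power with all 300 patients.** At 0.3 SD, simulated power was 73.7% against 75.3% (r = 0.05) and 74.1% against 77.6% (r = 0.10). At the design difference of 0.5 SD it is above 99% either way.

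**5. A less tidy design.** The exact balance in steps 2 to 4 is an idealisation. A further simulation took 300 patients, blocks of 4 within centre (assumed), about half the patients in each disease group, and 15% random loss. Type I error without centre was about 4.8% and 4.3% for the overall comparison at shares of 5% and 10%. Within one disease group it was 4.9%, 4.5% and 4.4% at shares of 5%, 10% and 15%, with a power gain from adjustment of about 1, 3 and 5 points. The distortion is smaller there because no blocking by disease is described, so nothing forces the arms to balance by centre inside a disease group.

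**The case against.** Four arguments can be made against the point.

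- **Model terms belong in the analysis plan.** This is a condensed article, and the ANOVA named for the main hypothesis is not said to be one-way. With only two arms, post-hoc tests make sense only if the model has another factor, so centre is not excluded. This stands for that ANOVA. It does not rescue Kruskal-Wallis, the one-way ANOVA, the t-test or the ordinary chi-square, which cannot carry a blocking factor as named.
- **Multilevel regression is planned and could hold centre as a level.** It could, but the article does not say so and does not make that model decide the hypothesis.
- **Blocking within centre is not stated outright.** True. It is the natural reading of the sentence, and the result depends on it.
- **The effect may be nil.** The comparison is of change from baseline, which removes stable differences in level between centres and so may take away part of r. This stands.

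A reader might also infer that all four listed tests are confirmatory, that they certainly compare arms without centre, and that the standard errors are therefore wrong as a matter of fact. The documents do not support that. Only ANOVA and Kruskal-Wallis are tied to the main hypothesis, and the excess in the standard error exists only if outcomes differ between centres.

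**Conclusion.** The point holds in a limited form. Allocation is blocked by centre, and the tests that the article names do not use centre. To the extent that outcomes differ between centres, the unadjusted tests are mildly conservative. For the overall comparison the standard error is up to about 2.6% too large at a 5% share and 5.4% at 10%, and adjustment gains about 1 to 3 points of power where power is near 80%. At a share of 2% or less there is almost nothing to gain, and at 0.5 SD with all 300 patients the overall comparison has little power to lose.

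It would be wrong to conclude that the trial's inference is invalid. The estimate is not biased, false positives do not rise, and the sample size is unaffected. The figures rest on an assumed centre share, on blocking within centre, and on a continuous outcome. The recommendation is a free improvement of low severity.

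**What to change.** In the section on analysis of clinical efficacy, state that the model that confirms the main hypothesis includes centre (three levels) as a fixed factor, and name the levels of the multilevel regression. Where responder variables are compared, use a Cochran-Mantel-Haenszel test stratified by centre, or logistic regression with centre, in place of the ordinary chi-square. Where ranks are compared, use the van Elteren test stratified by centre in place of Kruskal-Wallis. Align the general list of tests under the cost-utility heading with this.

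The cost is wording only. Each patient's centre is already known from the randomization, no extra patients or data are needed, and the linear model spends two degrees of freedom.

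### The sample size relies on four arm-by-disease groups of 63, but quota and blocking are by centre only, so the 80% power within each disease is not secured

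*Protocol article*

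**What the plan says.** The Sample size section of the protocol article plans "for a difference in the main variable of at least 0.5 standard deviations", and at "a power of 80%, and a level of significance of 5%, 63 subjects were estimated for each group". It then extends the calculation so that the arms can be compared overall and also by disease group: "4 groups were estimated with 63 subjects in each one, with a total of 252 subjects". An allowance of 15% for loss brings the total to 300.

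Three other sections state how those 300 are obtained:

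- Setting and study sample: patients are recruited "with a quota of 100 patients assigned to each centre". Table 1 admits a patient with either condition and gives no target mix.
- Recruitment: "Recruitment will be done consecutively until the final sample sizes are reached". The only sizes given in this part of the article are per centre and per arm.
- Randomization, allocation and masking of study groups: "The randomization will be conducted by blocks of patients from the three PC centres", with 150 patients per arm in total.

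No section sets a number for diabetes or for low back pain, and none names disease as a stratification factor.

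**The concern.** A plain two-arm comparison needs 2 x 63 = 126 analysable patients by the article's own calculation. The step from 126 to 252 is justified only by the comparisons within each disease. Those extra patients serve that purpose only if they fall evenly into the two disease groups.

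Consecutive recruitment under a centre quota produces whatever mix the practices happen to refer. If one condition is more common among eligible patients, the other group falls short of 63 per arm, and a null result in it would say little. What is at stake is the reliability of the disease-specific results, which are the stated reason for the trial's size.

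**Working it through.** **Inputs.** From the Sample size section: difference 0.5 SD, equal variances, power 80%, significance level 5%, four groups, 15% loss, total 300. Sidedness is not stated; a two-sided test reproduces the stated figure. The disease mix is not in the article, so it is varied below as an assumption.

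**1. The plan's own figures.**

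- Per group: n = 2 x (1.960 + 0.842)² / 0.5² = 62.8, rounded up to 63. The exact t-test gives 63.8.
- Four groups: 4 x 63 = 252.
- With loss: 252 / 0.85 = 296.5, so 297. The stated 300 agrees with this after rounding.

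The arithmetic is sound.

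**2. Slack.** 300 x 0.85 = 255 analysable against 252 required. The smaller disease group must supply 2 x 63 = 126 of the 255, which is 126 / 255 = 49.4%. In randomized patients that is 126 / 0.85 = 148.2, so at least 149 of 300.

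**3. Power within the smaller disease group.** For share s, analysable patients per arm are 300 x s / 2 x 0.85. Power is for a two-sided t-test at 5% and 0.5 SD; the normal approximation, Φ(0.5 / √(2/n) − 1.96), is alongside.

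| Assumed share of smaller group | Analysable per arm | Power (t-test) | Power (normal) |
|---|---|---|---|
| 50% | 63.75 | 80% | 81% |
| 45% | 57.4 | 76% | 76% |
| 40% | 51 | 71% | 71% |
| 30% | 38.25 | 58% | 59% |
| 20% | 25.5 | 42% | 43% |

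**4. Total needed without a quota.** To keep 63 analysable per arm in the smaller group, N = 126 / (s x 0.85): 371 at 40%, 495 at 30%, 742 at 20%.

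**5. Overall comparison.** There are 150 x 0.85 = 127.5 analysable per arm. √(2/127.5) = 0.125, and Φ(0.5 / 0.125 − 1.96) is about 98%. This does not depend on the mix.

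**6. Missing stratification on its own.** If the disease mix is fixed but allocation ignores disease, the number of a disease group's patients falling in one arm follows a hypergeometric distribution. The 95% ranges are 67 to 83 of 150, 37 to 53 of 90, and 23 to 37 of 60. Power at those limits, against an even split (normal approximation), is 80.1% against 80.6%, 57.6% against 59.0%, and 41.1% against 43.1%. The loss is at most about 2 percentage points.

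**The case against.** The strongest reply is that the main hypothesis is a single comparison of two arms, stated in the Abstract and at the end of the Background, and that the Analysis strategy describes a head-to-head comparison of the two groups. The within-disease comparison appears in the Sample size section alone. This stands, and it limits the consequence. A reader might take 42% to 71% as the power of the trial; it is not, because the primary two-arm comparison keeps about 98%.

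Two further readings are tempting and are not supported:

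- Because disease decides which physical measures enter the composite, a reader might infer that uneven disease numbers between the arms would confound the primary outcome. Under randomization such unevenness is chance variation, not systematic bias, and step 6 shows that its likely size is modest.
- A reader might infer that the trial is sized to test whether the effect differs between diseases, and fault its power for that. The article's phrase, "as well as depending on the conglomerate to which they belong (each disease group"), is loose, but it names no interaction test, so there is no such claim to fault.

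It can also be said that a condensed article may omit operational recruitment caps. That carries less weight here, because the article does state its quota and its blocking, and both are by centre. Finally, the disease shares are assumptions. A mild departure such as 45:55 costs only about 4 points; the shortfall is serious only if the mix is clearly skewed.

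**Conclusion.** The point holds for the comparisons within each disease. The Sample size section depends on four groups of 63, and the stated quota, recruitment rule and blocking do not secure them. With three analysable patients to spare (255 against 252), the stated 80% within each disease holds only at a split very close to 50:50. If the smaller group is 40%, 30% or 20% of patients, power within it is about 71%, 58% or 42%.

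These figures assume 0.5 SD, a two-sided 5% test, 15% loss spread evenly over the groups, and equal arms within each disease. The mix itself is unknown. The missing quota accounts for nearly all of the shortfall; missing stratification adds little. The overall comparison is unaffected. This should be corrected, but it does not put the main hypothesis in doubt.

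**What to change.** Set a recruitment quota by disease group, 150 per disease (for example 50 per disease at each centre), and stratify the blocked randomization by centre and disease group. With the same 300 patients this gives 75 randomized and 63.75 analysable per group, which meets the stated 80%. State which stratum takes a patient who has both conditions: the composite weights of one third or one half in the Main outcome section suggest that such patients may be enrolled, and the four-group plan gives them no place.

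The cost is a new randomization list with six strata and a recruitment cap. The downside is that one disease group may close early at a centre and slow recruitment.

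If a quota is not practicable, reword the Sample size section so that it no longer implies 80% power within each disease group. Base the total on the overall comparison and present the disease-specific results as estimates whose precision depends on the mix recruited. That costs only a text change.
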